# A randomized double-blind placebo-controlled trial to investigate the effects of nasal calcitonin on bone microarchitecture measured by high-resolution peripheral quantitative computerized tomography in postmenopausal women — Study protocol

**DOI:** 10.1186/1745-6215-9-19

**Published:** 2008-04-13

## Abstract

**Background:**

Bone microarchitecture is a significant determinant of bone strength. So far, the assessment of bone microarchitecture has required bone biopsies, limiting its utilization in clinical practice to one single skeletal site. With the advance of high-resolution imaging techniques, non-invasive in vivo measurement of bone microarchitecture has recently become possible. This provides an opportunity to efficiently assess the effects of anti-osteoporotic therapies on bone microarchitecture. We therefore designed a protocol to investigate the effects of nasal salmon calcitonin, an inhibitor of osteoclast activity, on bone microarchitecture in postmenopausal women, comparing weight bearing and non-weight bearing skeletal sites.

**Methods:**

One hundred postmenopausal women will be included in a randomized, placebo-controlled, double-blind trial comparing the effect of nasal salmon calcitonin (200 UI/day) to placebo over two years. Bone microarchitecture at the distal radius and distal tibia will be determined yearly by high-resolution peripheral quantitative computerized tomography (p-QCT) with a voxel size of 82 μm and an irradiation of less than 5 μSv. Serum markers of bone resorption and bone formation will be measured every 6 months. Safety and compliance will be assessed. Primary endpoint is the change in bone microarchitecture; secondary endpoint is the change in markers of bone turnover.

**Hypothesis:**

The present study should provide new information on the mode of action of nasal calcitonin. We hypothezise that - compared to placebo - calcitonin impacts on microstructural parameters, with a possible difference between weight bearing and non-weight bearing bones.

**Trial Registration:**

ClinicalTrials.gov NCT00372099

## Background

Osteoporosis is characterized by compromised bone strength and higher fragility, resulting in an increased fracture risk [1]. The measurement of areal bone mineral density (BMD) by dual-energy X-ray absorptiometry (DXA) is the most common way to measure bone mass and to assess fracture risk. Yet, bone strength is also determined by bone geometry, bone microarchitecture, bone remodelling and intrinsic tissue quality [2]. Thus, it is not surprising that BMD only partially explains the variance of strength and fracture risk [3]. It has been postulated that markers of bone remodelling determined in blood or urine could be independent predictors of fracture risk [4]. Assessment of changes in bone microarchitecture has been limited, since bone biopsies were necessary to investigate these parameters in the past. This technique is limited to a non-weight bearing bone such as the iliac crest. Today, high-resolution peripheral quantitative computerized tomography (p-QCT) allows an efficient and quantitative evaluation of bone microarchitecture [5,6]. It determines in three dimensions true volumetric density (g/cm^3^), and can directly assess trabecular thicknesses, trabecular separations, and trabecular number, and also provides additional geometric variables such as cross-sectional area (CSA) and information on structural pattern (rod vs. plate structure) with a relatively low irradiation, high accuracy and precision [7]. P-QCT thus provides a unique non-invasive opportunity to explore the effects of diseases on bone microarchitecture and of therapies intended to halt or reverse these changes [8].

Postmenopausal bone loss and fracture risk are associated with an imbalance in bone turnover. As a therapeutic agent, calcitonin binds to specific receptors on the osteoclasts and reduces their relative hyperactivity.

The formula of nasal calcitonin is well tolerated. The most common side effects consist of mild or moderate rhinitis symptoms, such as nasal congestion and sneezing, or nasal dryness [9,10]. Rarely, hypersensitivity reactions may occur.

Prolonged administration of intranasal calcitonin can prevent postmenopausal bone loss and is also able to increase trabecular bone mass among patients presenting established osteoporosis [10,11]. It has been demonstrated that the prolonged daily administration of 200 IU intranasal calcitonin inhibits bone resorption, increases lumbar spine BMD by 1.7%–3.3% after one year, and reduces vertebral fracture risk [9,12]. Furthermore, specific modification of bone microstructure was demonstrated at the distal radius using magnetic resonance imaging [13].

A possible effect of calcitonin on bone microarchitecture could be investigated using high-resolution p-QCT. By assessing structural bone changes, the present study should thus provide new insights in the mode of action of nasal calcitonin. We hypothezise that - compared to placebo - calcitonin improves or maintains microstructural parameters, with a possible difference between weight bearing and non-weight bearing bones.

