### Efficacy assessments

#### Bone microarchictecture measurements

Bone microarchitecture will be investigated by p-QCT at baseline and after one and two years. Three-dimensional high-resolution measurements will be performed at the distal radius and tibia using an Xtreme CT device (Scanco Medical AG, Bassersdorf, Switzerland), as described by others [15]. In brief, the non-dominant limb (or the nonfractured limb in case of prior fractures) will be scanned at the standardized locations for human in vivo measurements. The following settings are used: effective energy of 60 kVp, matrix size 1536 × 1536, x-ray tube current 900 μA, slice increment 82 μm. One hundred and ten slices will be obtained with a voxel size of 82 μm. The effective dose for one Xtreme CT standard measurement is 3 μSv per site. Processing of the obtained scans will be done in accordance with the default protocol of the device. Table 3 lists the assessed bone parameters. In our institution, the in-vivo coefficient of variation (CV%) for these bone indices ranges from 0.5 – 1% (vol. densities) to 3 – 5% (TbN). Quality control is performed on a daily basis.

**Table 3 T3:** Parameters of bone microarchitecture

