### Statistical methods

#### Sample size calculation

A total number of 80 patients (40 in the calcitonin group and 40 in the control group) is necessary to have a statistical power of 80% to detect an expected difference of 3.5% in BV/TV [13]. Due to an expected drop-out rate of 20%, a total of 100 patients should be enrolled.

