#### Statistical analysis

Data will be summarized with respect to demographic and baseline characteristics, efficacy observations and measurements, and safety observations and measurements.

To assess the treatment effects of calcitonin on bone microarchitecture and provide a proof of concept, the primary analysis of the efficacy endpoints in this exploratory trial will be based on the observed data of the per-protocol population. Secondarily, an ITT analysis may be performed to test the robustness of the results.

For each analyzed parameter a two-sided t-test will be applied. The change from baseline between the two different groups (active treatment/placebo) will be compared by an analysis of covariance (ANCOVA) model with change as the response variable, the baseline value as a covariate, and treatment as a fixed factor.

The assessment of safety will be based mainly on the frequency of adverse events and on the number of laboratory values that fall outside of pre-determined ranges. Other safety data (e.g. electrocardiogram, vital signs, special tests) will be considered as appropriate.

Analysis of adverse events will be based on the safety population which includes all randomized patients who have taken at least one dose of the study drug. Adverse events will be summarized by presenting, for each treatment group, the number and percentage of patients having any adverse event, having an adverse event in each body system and having each individual adverse event. Any other information collected (e.g. severity or relatedness to study medication) will be listed as appropriate.

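### The aim includes comparing calcitonin's effect at the tibia and the radius, but the stated analysis contains no contrast between the two sites

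*Protocol article*

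**What the plan says.** The site comparison appears in the aim and in the hypothesis. The abstract's Background gives the purpose as studying nasal calcitonin "comparing weight bearing and non-weight bearing skeletal sites". The Hypothesis paragraph of the abstract and the last paragraph of the Background both expect an effect against placebo "with a possible difference between weight bearing and non-weight bearing bones".

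Both sites are measured. Under Bone microarchitecture measurements: "Three-dimensional high-resolution measurements will be performed at the distal radius and tibia using an Xtreme CT device". Table 2 places the pQCT scans at baseline, month 12 and month 24.

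Statistical analysis states: "For each analyzed parameter a two-sided t-test will be applied". Change from baseline is then compared between arms by ANCOVA "with change as the response variable, the baseline value as a covariate, and treatment as a fixed factor". The same section calls the trial exploratory: "the primary analysis of the efficacy endpoints in this exploratory trial will be based on the observed data of the per-protocol population". The sample size is chosen "to have a statistical power of 80% to detect an expected difference of 3.5% in BV/TV", with 40 women per arm and 100 enrolled to allow for 20% drop-out. That sentence names no site.

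**The concern.** A difference in effect between tibia and radius is a treatment-by-site interaction. The stated model has treatment and the baseline value on the right-hand side and is fitted to one parameter at a time. It gives one between-arm result at the radius and another at the tibia, and nothing that compares them.

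Setting the two results side by side does not fill the gap. A significant result at one site and a non-significant one at the other is common when the true effects are equal, because each site's test has its own sampling error and less than full power. At stake is one of the trial's own questions. It would have no estimate attached, and a chance pattern could be taken for a mechanical-loading effect. Table 3 lists twelve parameters, which gives that pattern many opportunities to appear.

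**Working it through.** **Inputs from the article.** 40 evaluable women per arm, 80% power and a 3.5% difference in BV/TV (Sample size calculation); two-sided tests (Statistical analysis); both sites scanned (Bone microarchitecture measurements).

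**Inputs assumed because the article does not give them.** Alpha 0.05; the same SD of change at both sites; the 3.5% read as absolute points; 80% power at each site; correlation ρ between radius and tibia changes within a woman, from 0 to 0.8.

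**Step 1: the plan's own figure.** 80 / (1 − 0.20) = 100, so the enrolled total reproduces. The 40 per arm cannot be checked without an SD. Solving for the SD that makes it correct:

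SD = 3.5 × √(40/2) / (1.960 + 0.842) = 5.59 points (5.52 with the noncentral t).

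**Step 2: equal true effects, separate tests.** The two site z-statistics are bivariate normal with common mean 1.960 + 0.842 = 2.80 and correlation ρ. Then

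P(exactly one significant) = 2 × [0.80 − P(both significant)].

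At ρ = 0 this is 2 × 0.80 × 0.20 = 0.32. For other ρ, the joint probability comes from the bivariate normal distribution. The calculation was repeated with 50% power at each site.

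**Step 3: the direct contrast.** The standard error of one site's effect is 5.59 × √(2/40) = 1.249. The difference between the two paired site effects has

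SE = 1.249 × √(2(1 − ρ)).

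Power for a true difference D is Φ(D/SE − 1.96) + Φ(−D/SE − 1.96). At ρ = 0, SE = 1.767. With D = 3.5, D/SE = 1.98 and power is 51%. With D = 1.75, D/SE = 0.99 and power is 17%.

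| Between-site correlation ρ | 0 | 0.3 | 0.5 | 0.7 | 0.8 |
|---|---|---|---|---|---|
| Exactly one site significant, equal effects, 80% power each | 32% | 27% | 23% | 17% | 14% |
| Same, 50% power each | 50% | 40% | 33% | 25% | 21% |
| False-positive rate of the direct test | 5% | 5% | 5% | 5% | 5% |
| SE of the contrast (points) | 1.77 | 1.48 | 1.25 | 0.97 | 0.79 |
| Power, site difference 3.5 points | 51% | 66% | 80% | 95% | 99% |
| Power, site difference 1.75 points | 17% | 22% | 29% | 44% | 60% |

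The approximate 95% CI half-width is 1.96 × 1.77 = 3.5 points at ρ = 0 and 1.96 × 0.79 = 1.5 points at ρ = 0.8.

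**How far the assumptions matter.** The rates of one-site significance depend on the power at each site and on ρ, not on the SD itself. The powers depend on D as a fraction of the planned effect, because the SD was solved from that effect. Unequal SDs, or unequal power at the two sites, would change the figures.

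**The case against.** The strongest objection is that a journal article condenses the full protocol, and a site contrast for a subsidiary question could sit in an analysis plan that is not shown. The article does not exclude one. The site difference is also hedged as only possible. It is absent from the End points section, the sample size and the Summary, and the trial is labelled exploratory. This stands as a limit on weight and scope: the finding concerns this article's stated analysis, not everything the trial may do. It does not remove the mismatch. The article spells out the response, covariate and fixed factor, and they do not fit a comparison that it names in its aim and hypothesis.

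A reader might go further and infer that the investigators intend to claim a site-specific effect whenever one site is significant and the other is not, so that 14% to 32% becomes the plan's own error rate. The article does not support this. It states no rule for reading a one-site result and does not say that p-values will be compared across sites. The percentages describe what would happen if someone read the results that way.

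The figures also rest on unstated quantities. In particular, the sample size cites the same source that the Background cites for a finding at the distal radius, so 80% power at the tibia is not documented.

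Finally, the direct test is weak for moderate differences. That is true, and it argues against making the contrast a confirmatory gate. It also argues for an estimate with an interval, since two separate significance results carry even less information about the difference.

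**Conclusion.** The concern holds as a mismatch between aim and analysis. The tibia-radius comparison is part of the stated purpose and hypothesis, and the stated per-parameter test and ANCOVA contain no contrast between sites.

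If results were read site by site, exactly one site would be significant in about 14% to 32% of trials with identical true effects, against 5% for a direct test. This assumes two-sided alpha 0.05, equal SDs, 80% power at both sites and a between-site correlation from 0.8 down to 0; the article gives neither the alpha, the SDs, the correlation nor the power at each site. Lower power per site makes the pattern more frequent. The supportable statement is that such results could be misread, not that they will be. Given the exploratory label and the hedged hypothesis, this is a worthwhile improvement and not a defect that undermines the main comparison with placebo.

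**What to change.** Before unblinding, pre-specify one exploratory treatment-by-site contrast for BV/TV at month 24. For each woman, take tibia percent change minus radius percent change and compare it between arms, adjusting for both baseline BV/TV values. A mixed model with site, treatment and treatment-by-site, and woman as a random effect, is an alternative. The two can differ when one site's scan is missing, so the plan should name one. It should also name the scale, because an interaction depends on it and the sample-size section does not say whether 3.5% is absolute or relative.

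Report the difference in effects with its 95% CI, labelled exploratory. Base any statement about a site difference on that estimate and not on significance at one site only.

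The cost is a sentence or two in the plan and one extra model; no scan, visit or participant is added. The downside is low power, about 17% to 60% for a difference half the planned effect. The plan should say in advance that a wide interval is expected and that an inconclusive result does not show the sites to be alike.

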## Methods

### Study design

This is a monocentric, randomized, placebo-controlled, double-blind trial over two years, assessing the effects of nasal calcitonin (200 IU/day) on bone microarchitecture measured by high resolution p-QCT in postmenopausal women.

This protocol was initiated by the principal investigator and has been accepted by the ethics committee of the University Hospitals of Geneva and by the Swiss legislative authority (Swissmedic). It has been registered in a public clinical trial data base [ClinicalTrials.gov number NCT00372099] [14].

### End points

Primary efficacy endpoint will be changes in bone structure and bone microarchitecture evaluated by high resolution p-QCT in postmenopausal women compared to placebo during two years.

As a secondary endpoint we will investigate changes in markers of bone turnover.

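### The primary endpoint is a whole domain of p-QCT measures with no parameter, site or time point named, and BV/TV, which sized the trial, is not designated primary

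*Protocol article*

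**What the plan says.** All references are to the protocol article.

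- **End points:** "Primary efficacy endpoint will be changes in bone structure and bone microarchitecture evaluated by high resolution p-QCT". The sentence closes with its population, its comparator and its only reference to timing: "in postmenopausal women compared to placebo during two years". The Abstract gives the same endpoint in shorter form. Neither place names a variable, a site or a visit.
- **Bone microarchitecture measurements:** "Table 3 lists the assessed bone parameters". The table has five densities and seven structure variables. Two sites are scanned: "Three-dimensional high-resolution measurements will be performed at the distal radius and tibia". There are two follow-up scans: "Bone microarchitecture will be investigated by p-QCT at baseline and after one and two years".
- **Statistical analysis:** "For each analyzed parameter a two-sided t-test will be applied". Change from baseline "will be compared by an analysis of covariance (ANCOVA) model with change as the response variable", with baseline as covariate and treatment as factor. The section calls the trial exploratory and a proof of concept. It ranks no parameter above another and gives no significance level.
- **Sample size calculation:** 40 patients per group give 80% power "to detect an expected difference of 3.5% in BV/TV". No site, time point or standard deviation accompanies this figure, and BV/TV is not called the primary variable.

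**The concern.** A primary endpoint should tell the reader, before the data are seen, which comparison answers the trial's question. Here the label covers a set of variables, and the one variable that was sized carries no special status in the endpoint or analysis sections. If BV/TV shows nothing but, say, cortical thickness at the tibia gives a small p-value, the plan as written allows the latter to be reported as the primary finding.

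The error rate of a claimed effect on microarchitecture is then that of the whole set of tests, not of one test. A reader of the results could not tell a real effect on one parameter from the best of many chance results.

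**Working it through.** **The plan's own figures.** The dropout step reproduces: 80 / (1 − 0.20) = 100. The 80 itself cannot be checked, because neither the standard deviation (SD) nor the significance level is given. Assuming a two-sided 5% level, the SD of change that gives 80% power with 40 per group is

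SD = 3.5 / [(1.960 + 0.842) × √(2/40)] = 3.5 / 0.626 = 5.6 percentage points,

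or 5.5 with the t distribution (standardized difference 0.634).

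**Counting the comparisons.** Parameters: 5 + 7 = 12 (Table 3). Sites: 2. At month 24 alone, 12 × 2 = 24 tests. If month 12 also counts, 12 × 2 × 2 = 48.

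**Independent tests at an assumed 5% each.** The chance of at least one p < 0.05 with no true effect is 1 − 0.95^m:

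- m = 24: 1 − 0.95^24 = 0.708
- m = 48: 1 − 0.95^48 = 0.915

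The expected number of nominally significant results with no true effect is 24 × 0.05 = 1.2 or 48 × 0.05 = 2.4, whatever the correlation.

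**Correlated tests.** The parameters come from the same scans, so independence is an upper bound here. The article gives no correlations, so a range is assumed: 0.3 to 0.8 between parameters, 0.3 to 0.7 between sites, and 0.6 between the two years. Normal test statistics were simulated with these correlations multiplied across the three dimensions, counting draws in which the largest absolute value exceeded 1.96. Because the tests are two-sided, reversing the sign of a parameter (separation against number, for example) changes nothing.

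| Between parameters | Between sites | 24 tests | 48 tests |
|---|---|---|---|
| 0.3 | 0.3 | 63% | 83% |
| 0.3 | 0.7 | 58% | 78% |
| 0.5 | 0.5 | 51% | 72% |
| 0.7 | 0.5 | 38% | 58% |
| 0.8 | 0.3 | 33% | 50% |
| 0.8 | 0.7 | 29% | 45% |

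A harsher assumption gives every pair of tests the same correlation, across sites and years as well. At 0.3, 0.5 and 0.8 the chance is then 59%, 46% and 24% for 24 tests, and 80%, 61% and 30% for 48.

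**With one named variable.** One parameter, one site and one time point bring the error back to the assumed 5%, and the planned 80% power stands. If both sites were co-primary at 0.05/2 = 0.025 each, power per site would be about 71% with 40 per group, assuming the same standardized difference at both sites.

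**The case against.** The strongest reply is that the trial is declared exploratory. Its hypothesis concerns microstructural parameters in the plural, with a possible difference between weight-bearing and non-weight-bearing bone. Strict family-wise control is not obligatory in such a trial. Adjustment methods and test order are also commonly left to an analysis plan, which is not at hand. This stands in part: the lack of a stated multiplicity procedure is not, by itself, a fault of this article. But the exploratory label does not say which result is primary. The same article declares a primary endpoint, specifies a primary analysis and claims 80% power for one variable, and those statements fit together only if that variable is designated.

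Three stronger readings might be inferred, and the article does not support them.

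- **A false-positive primary result is more likely than not.** This is conditional. It fails for 24 tests once the correlation between parameters exceeds about 0.5, and for 48 tests at about 0.8. High correlation is credible: Table 3 lists trabecular density beside its meta and inner regions, and several indices describe one trabecular network. The figures also rest on a 5% level that the article never states.
- **There are 48 primary tests.** Counting month 12 is one reading of "in postmenopausal women compared to placebo during two years". The article does not say that the one-year comparison is primary.
- **The stated power applies to nothing.** The sample size section ties it to BV/TV. What is missing is the site, the time point and the designation as primary.

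**Conclusion.** The defect is real: the primary endpoint is a domain, every parameter in it gets its own test, the sized variable is not designated primary, and no other part of the article settles the matter.

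Its size depends on two assumptions that the article does not supply, a two-sided 5% level and the correlations. Within the range examined with separate parameter, site and year correlations, the chance of at least one false-positive result that could be called primary is about 29% to 63% for the 24 month-24 tests (71% if independent). It is about 45% to 83% if month 12 is included (91% if independent). The lowest of these is nearly six times 5%. Even under one common correlation of 0.8 across all 24 tests, it is 24%.

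**What to change.** Before unblinding:

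1. State the significance level.
2. Name change in BV/TV from baseline to month 24, at one site, as the sole primary variable. BV/TV is the sized variable, and month 24 is the end of the two-year trial. The distal radius is the site with most support: the source cited for the 3.5% is the magnetic resonance imaging study that the Background credits with showing microstructural change there.
3. Test BV/TV at the distal tibia next in fixed sequence, at the full level and only if the radius test is significant. Radius first is not the only defensible order, given the interest in weight-bearing bone. Making both sites co-primary with a stated split of the significance level is an alternative, at the lower power per site shown above.
4. Label all other Table 3 parameters and all month-12 results secondary or exploratory, reported with estimates and confidence intervals.

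**Cost.** Recruitment began in January 2007, and the protocol is already accepted by the ethics committee and the regulator and publicly registered, so expect a protocol amendment and a registry update. No further patients or scans are needed, and the sample size stands if BV/TV at one site and one time point is primary. The price is that significant results in other parameters can no longer be presented as the primary result.
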